## 4. Interventions

The intervention will be conducted in healthcare facilities that provide inpatient and outpatient care for chronic HF. The intervention will be carried out by HF nurses or nurses with at least 3 years of experience in HF nursing. The intervention period is set for three months after discharge, with a focus on the first month as a period of intensive support (Figure 1).

On the third day after discharge, support is provided via phone to the patient and their family to confirm their living situation, medication adherence, and self-management status related to weight and blood pressure control. If the patient was discharged to a facility, information is gathered from the facility staff and nursing consultation and guidance is provided to the patient and staff. In-person support for approximately 30 min is provided at the first outpatient visit after discharge (usually about 2 weeks later). For one month after discharge, support is provided once a week via in-person or phone methods. Following the initial month where support is provided weekly, both in-person and phone support will be offered once a month for the next three months. Depending on the patient’s condition and the judgment of the nursing staff, additional support may be provided as needed.

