## 5. Control

During hospitalization, the usual medical care and discharge instructions according to the patient’s condition are provided, in the same manner as for the intervention group. In the outpatient setting, routine outpatient visits and care are also provided in each medical institution. The usual care is based on the concept of self-monitoring for HF patients and follows the disease-management program outlined within the heart failure guideline in Japan. Therefore, patient education during hospitalization is conducted appropriately, specifically including providing education to HF patients on self-monitoring their symptoms and other findings. However, regarding post-discharge care, even if the environment for structured nurse interventions is available, these are not implemented in the control group, in order to ensure a clear distinction between the intervention and usual care [19].

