In the intervention group, the same set of items as the baseline data, such as symptom control status, self-care behavior, self-reported symptoms and signs, and social circumstances will be collected at occurrence of readmission due to HF within 30 days or 3 months after discharge. The reason for readmission and duration of home care until readmission are collected. In addition, to capture the status of the intervention, the number of outpatient visits, including unscheduled visits, and the dates, times, and number of sessions by telephone and in-person are noted. If there are unscheduled teaching sessions, their content is also noted in the record. If the intervention has resulted in avoidance of hospitalization due to early visit or adjustment of oral medications, this should be reported.

In the control group, the same set of items as in the baseline data will be collected at 3 months after discharge. As with the intervention group, occurrence of readmission due to HF within 30 days or 3 months after discharge, and the reason for readmission and duration of home care until readmission are noted. Additionally, the number of outpatient visits (scheduled and unscheduled), and whether or not face-to-face medical guidance was provided are determined. If so, date, time, face-to-face time and content are collected.

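### Follow-up triggers and scheduled contact differ by arm, and no common source or schedule is given for finding HF readmissions, so they may be ascertained unequally

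*Protocol article*

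**What the plan says.** All references are to the protocol article.

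- **Follow-up trigger, intervention arm (Section 6).** The repeat of the baseline items, including self-care behavior, "will be collected at occurrence of readmission due to HF within 30 days or 3 months after discharge".
- **Follow-up trigger, control arm (Section 6).** "In the control group, the same set of items as in the baseline data will be collected at 3 months after discharge".
- **Readmission fields (Section 6).** For the intervention arm: "The reason for readmission and duration of home care until readmission are collected". For controls: "As with the intervention group, occurrence of readmission due to HF within 30 days or 3 months after discharge", with reason and time at home, is noted. Neither sentence says from what source, by whom or when a readmission is to be discovered.
- **Scheduled contact, intervention arm (Section 4).** There is a phone call on day 3 to patient and family, or contact with facility staff. Then: "For one month after discharge, support is provided once a week via in-person or phone methods". After that, "both in-person and phone support will be offered once a month for the next three months".
- **Scheduled contact, control arm (Section 5).** Routine outpatient visits continue. Of structured nurse interventions after discharge, the text says that "these are not implemented in the control group", even where a site could provide them.
- **Conduct.** Investigators and participants are not blinded (Section 2.5), and local researchers and nurses collect the data (Section 7).
- **Use of the outcome.** HF readmission at 30 days, 3 months, 6 months and 1 year, and time at home until readmission, are secondary outcomes (Section 3.2). Section 8 plans Kaplan-Meier, log-rank and Cox analyses.

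**The concern.** A between-arm comparison of readmission needs each arm to have the same chance of having an event found. Here the intervention nurse speaks to the patient, family or facility staff repeatedly by design. The control site has only routine visits and one stated collection point. Since whole facilities are randomized, any difference in how sites learn of events coincides with arm.

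The eligible population sharpens this. Section 2.7 selects patients with problems such as living alone, weakened family support, cognitive impairment or missed appointments. A control patient of this kind who is admitted elsewhere may not report it, and the routine visit at which it might emerge is one that some of them miss.

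The planned analysis would not repair a difference. A readmission that nobody learned of is recorded as no event, not as missing, so multiple imputation does not reach it. Covariate adjustment and propensity scores do not recover it either. The primary outcome, EHFScBS, is not touched by this point. HF readmission is nonetheless part of the aim stated in the Abstract and of the purpose in Section 10, and Section 9 says that the results are meant to support policy recommendations.

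**Working it through.** The plan gives no readmission rate and no ascertainment rate, so there is no stated figure to reproduce. The check is a comparison of the text by arm, followed by a scale calculation on assumed capture shares.

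**Step 1. The two arms side by side**

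| Feature | Intervention | Control |
|---|---|---|
| Trigger for repeat item set (Section 6) | HF readmission | Fixed 3 months |
| Readmission fields and windows (Section 6) | Occurrence, reason, time at home; 30 days and 3 months | The same |
| Source or schedule for finding readmissions | None stated | None stated |
| Structured contact after discharge (Sections 4, 5) | Day 3, weekly for a month, then monthly | None; routine visits only |
| Data collectors (Section 7) | Local, unblinded | Local, unblinded |

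What is recorded about a readmission is the same. The follow-up trigger and the opportunity to learn of an event differ. An event-triggered form also works only if the site hears of the event.

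**Step 2. Effect on the risk ratio**

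Let c_I and c_C be the shares of true readmissions that are found in each arm, with no false positives. Then

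observed RR = true RR × c_I / c_C.

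The base rate cancels. The capture shares are assumptions: c_I = 1.00, and c_C = 0.95, 0.90 or 0.80. Two of the true RRs are figures that Section 10 cites: 0.85 (HF hospitalization, review of structured telephone support) and 0.60 (HF readmission, review of eight nurse-led trials). The third, 1.00, is no effect.

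| True RR | c_C = 0.95 | c_C = 0.90 | c_C = 0.80 |
|---|---|---|---|
| 1.00 | 1.05 | 1.11 | 1.25 |
| 0.85 | 0.89 | 0.94 | 1.06 |
| 0.60 | 0.63 | 0.67 | 0.75 |

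For example, 0.85 × 1.00 / 0.90 = 0.94. A true RR of 0.85 reaches 1.00 when c_C = 0.85, that is, when 15% of control events are missed.

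**Step 3. Direction**

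More contact in the intervention arm points to c_I > c_C, which biases against the intervention. The text does not settle it, because Section 6 states no fixed 3-month collection for the intervention arm. If events were missed there instead, say c_I = 0.90 and c_C = 1.00, a true RR of 0.85 would be observed as 0.85 × 0.90 = 0.77, in favor of the intervention.

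**The case against.** The strongest reply is that the text does not describe unequal detection. The sentence behind "will be collected at occurrence of readmission due to HF within 30 days or 3 months after discharge" governs when the item set is filled in, not how a readmission is discovered. For readmission itself Section 6 refers controls expressly to the intervention arm and uses the same fields and windows. A reader might infer that control readmissions are found only by a look-back at 3 months. The document does not say so: the fixed 3-month timing belongs to the item set.

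The sites also limit the problem. Every facility gives inpatient and outpatient care (Section 2.4), so a return to the index hospital should be visible in both arms. Control patients attend routine visits, and "the number of outpatient visits (scheduled and unscheduled), and whether or not face-to-face medical guidance was provided are determined". The mechanism therefore needs an admission elsewhere that also goes unmentioned, and the documents give no frequency for that. Finally, this is a condensed article: the detailed source for readmission data may stand in the full protocol, and Figure 1, which is said to show survey timing, is not visible.

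Most of this stands, and it narrows the point to readmissions outside the index hospital and to a possible rather than a demonstrated imbalance. It does not remove the point. The likeness asserted for controls concerns what is noted, and the intervention arm has no stated arm-neutral method for controls to share. Nor is this only missing detail: the article itself sets different follow-up triggers and different contact by arm.

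**Conclusion.** The concern holds in a limited form. As written, the plan pairs arm-specific follow-up triggers and much more scheduled contact in one arm with open-label local data collection, and states no common way of finding readmissions. HF readmissions, mainly those to other hospitals, may be ascertained unequally. Under-detection in controls is the more likely direction and would bias the readmission rate, Kaplan-Meier and Cox results against the intervention.

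The size cannot be derived from the documents. The figures above rest wholly on assumed capture shares. They show only that a shortfall of 10% to 15% in control capture would be about as large as the telephone-support effect that the article cites. A reader might conclude that control readmissions will be missed, or that a real benefit will vanish; the documents support neither. The outcome is secondary, so this should be corrected but does not threaten the primary comparison.

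**What to change.** In Section 6, state one ascertainment step for every patient in both arms, at 3 months and at each later horizon that is kept from Section 3.2:

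1. The same search of the facility's own records.
2. The same fixed question to patient or family about admission to any hospital since discharge.
3. Dates confirmed from records.

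Keep every record-verified readmission in the between-arm analysis, however it was learned of, and record how each was first learned of. Add a sensitivity analysis limited to events found through the common step. The main analysis should not be restricted in that way: it would discard verified readmissions in patients who die, drop out or cannot recall, and Section 2.3 assumes 30% dropout over one year.

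The cost is a little local staff time and some recall error. That error need not be equal between arms, since repeated nurse contact may aid recall, so confirmation from records is part of the step.

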## 7. Data Collection and Management

Data will be collected by the local researcher and nurses. Data will be coded and entered into either paper Case Record Forms or computer databases. Data entered on paper records will be sent directly to the Central Registration Center located at the Japanese Nursing Association. Data management will require two independent staff members in order to enter data into an Excel spreadsheet and have it saved onto a password-protected Universal Serial Bus mass storage device. Data management will also require double-checks for any potential errors in the input contents. Paper materials related to each participant’s evaluation will be stored in an evaluation binder, while intervention materials will be stored in a separate intervention binder. The binders holding evaluation and intervention forms will be kept inside a lockable shelf at Japanese Nursing Association and will be stored for up to 5 years after the examination ends.

## 8. Statistical Method

The Japan Nursing Association will submit the data received from the intervention and control groups’ medical institutions to a contracted data analysis organization for analysis. The between-group comparison of the change in self-care behavior continuity and changes in BNP and NT-proBNP in the baseline values at discharge and changes after intervention (1 and 3 months later) will be performed. The Spearman rank correlation coefficient will be used to measure the relationship between the scores of cardiac functions and the EHFScBS. The Mann–Whitney U-test will be used to compare the scores of the EHFScBS between the two groups with respect to patient backgrounds. The McNemar test will be used to analyze the changes in the two groups’ readmission and symptom deterioration rates, with the corresponding t-test employed for frequency, relative risk, and absolute risk reduction for risk difference. The presence or absence of readmission and the time to readmission between the intervention and control groups will be analyzed by the Kaplan–Meier method and tested for significance using the log-rank test. The Cox proportional hazard model and propensity score analysis will be used to compare between-group differences. Multiple imputation techniques will be employed to handle missing data, ensuring robustness and reducing bias in the findings. In the above analysis for the comparison, covariate adjustment from the baseline patient characteristics will be applied to gain efficiency in the estimation for the treatment effect, when it is necessary.

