## Abstract

Background: Heart Failure (HF) is a common chronic disease that has a high readmission rate and is associated with worsening symptoms and major financial impacts. Disease management implemented during or after an HF hospitalization has been shown to reduce hospitalization and mortality rates. Particularly for outpatients, it is necessary to provide self-care interventions. Structured nurse-led support such as timely follow-ups, including phone calls, is beneficial for improving self-care assessments. Evidence for nurse-led support has been investigated but is less than conclusive. The aim of this study is to compare the effectiveness of a nurse-led structured intervention for outpatients with chronic HF against the usual medical care in terms of self-care behaviors and occurrence of symptom exacerbation or rehospitalization. Methods and analysis: This is a cluster-randomized controlled trial. A total of 40 facilities with certified HF nurses will be allocated to two-arm clusters at a 1:1 ratio, randomly to the intervention or usual care arms. A total of 210 participants will be assigned from the hospital. Participants will be adults aged 18 years or older diagnosed with chronic HF who are classified as Stage C according to the ACCF/AHA Heart Failure staging system. In the intervention group, patients will receive structured nursing support. This begins with weekly support, including phone calls, for the first month, then transitions to monthly support thereafter. The aim is to ensure the stability of their living conditions, promote medication adherence, and encourage self-management. In the control group, patients will receive the usual care. Primary outcomes will assess the improvement or continuation of self-care behavior as measured by changes in EHFScBS (European Heart Failure Self-Care Behavior Scale) scores. Secondary outcomes include occurrence of readmission within 30 days, 3 months, 6 months, and 1 year after discharge, duration of home care until readmission, and blood levels of BNP and NT-proBNP.

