### 2.3. Sample Size

A sample size of 210 (105 in each arm) will allow us to detect a difference of four units in the EHFScBS scores with 80% statistical power. Assumptions are based upon data from the CHART-2 study, which estimated a mean clinical estimated difference of 4 in the EHFScBS before and after intervention, with a standard deviation of 8.5 [15,16]. The ICC was 0.05, and a dropout rate of 30% due to mortality or other reasons over one year was assumed, based on previous research results, in order to determine the sample size [17,18].

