## 3. Study Outcomes

### 3.1. Primary Outcomes

Self-care behavior improvement measured by EHFScBS. The Japanese version of the EHFScBS is a 12-item scale that uses a five-point response format, with lower total scores indicating better self-care behavior (range: 12–60); the questionnaire’s validity and the reliability of the Japanese version have been demonstrated [15].

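### The primary EHFScBS outcome has no named time point: Section 8 appears to compare it at both 1 and 3 months, and Section 6 does not give both arms the same fixed assessment

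*Protocol article*

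**What the plan says.** All references are to the protocol article.

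- Section 3.1 (Primary Outcomes) gives the outcome as "Self-care behavior improvement measured by EHFScBS", with the scale and its range but no time. The Abstract speaks of "improvement or continuation of self-care behavior as measured by changes in EHFScBS" scores, again with no time. Section 2.3 (Sample Size) powers the trial for a 4-unit difference and names no assessment time.
- Section 8 (Statistical Method) announces "The between-group comparison of the change in self-care behavior continuity" together with BNP and NT-proBNP, from baseline at discharge, and ends the sentence with "changes after intervention (1 and 3 months later) will be performed". It does not rank the two times, say whether both must succeed, or say how the significance level is shared.
- Section 6 (Data Collection) lists the EHFScBS among the baseline items. For follow-up it says: "In the control group, the same set of items as in the baseline data will be collected at 3 months after discharge". For the intervention arm the same set of items "will be collected at occurrence of readmission due to HF within 30 days or 3 months after discharge".
- The caption of Figure 1 says the figure shows when questionnaires are given in both groups. The figure itself is not available, and the caption lists no survey months.

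**The concern.** A primary outcome needs one time point, or a stated rule for combining several. Here the outcome definition gives none and the analysis section gives two. If both are tested and either may be reported as the primary result, the chance of a false claim exceeds the level of each test.

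The collection text does not settle the matter. It gives controls one fixed follow-up score, at 3 months. In the intervention arm, read literally, it gives a score only to patients readmitted for heart failure. If sites follow that wording, intervention patients who stay out of hospital have no fixed follow-up EHFScBS, and the arms are compared at different times and in differently selected patients. That would bias the primary comparison itself, which is a more serious matter than the error rate.

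**Working it through.** **Step 1. Set the sections side by side.**

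| Place | Time given for EHFScBS |
|---|---|
| Abstract, 2.3, 3.1 | none |
| 8 | 1 and 3 months, unranked |
| 6, control arm | 3 months after discharge |
| 6, intervention arm | at HF readmission within 30 days or 3 months (literal reading) |
| Figure 1 | not available |

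The only fixed follow-up time that Sections 6 and 8 share is 3 months, and Section 6 states it plainly for controls only. The text of Section 6 mentions no 1-month score in either arm.

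**Step 2. Reproduce the sample size, to see how many comparisons it covers.** Inputs from Section 2.3: difference 4, SD 8.5, power 80%, ICC 0.05, dropout 30%, N = 210. From the Abstract: 40 facilities, so 20 per arm. Alpha is not stated; two-sided 0.05 is assumed.

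- Per arm, before inflation: 2 × [8.5 × (1.960 + 0.842) / 4]² = 70.9.
- Evaluable patients per facility: 105 × 0.7 / 20 = 3.675. Design effect: 1 + 2.675 × 0.05 = 1.134. Then 70.9 × 1.134 = 80.4 per arm.
- Dropout applied as × 1.3: 104.5, so 105 per arm, or 210 in total. This matches exactly.
- With no design effect and dropout applied as ÷ 0.7: 101.3, so 102 per arm, or 204 in total. This is within 3%.

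Both routes use one comparison at the full 5%. With the level halved for two comparisons (0.025 each), the starting figure is 85.8 per arm. The totals then run from 224 (no design effect, × 1.3) to 298 (design effect 1.2125 for 5.25 enrolled per facility, ÷ 0.7). None gives 210.

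**Step 3. False-positive rate if both times are tested and either counts.** Let Z1 and Z2 be the two test statistics under no effect, with correlation ρ. The family-wise error is 1 − P(|Z1| ≤ 1.96 and |Z2| ≤ 1.96). At ρ = 0 this is 1 − 0.95² = 9.75%.

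| ρ (assumed) | two-sided | benefit direction only |
|---|---|---|
| 0 | 9.75% | 4.9% |
| 0.5 | 9.1% | 4.5% |
| 0.7 | 8.35% | 4.2% |
| 0.8 | 7.8% | 3.9% |
| 0.9 | 7.0% | 3.5% |

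The reference levels are 5% two-sided and 2.5% in the benefit direction.

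**Step 4. Cost of keeping both times with a Bonferroni split.** With 73.5 evaluable per arm (105 × 0.7), power at each time is 73% with no design effect, 67% with 1.134 and 64% with 1.2125. For one comparison at 5% the figures are 81%, 76% and 74%. Naming one time point is the cheaper course.

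**The case against.** Four points can be made for the plan.

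1. **Figure 1 may hold the schedule.** A reader might infer from Section 6 that 1-month control scores will not exist. The documents do not support that. The caption assigns survey timing to a figure that is not available here, and a 1-month survey may be in it. What stands is that Section 6 does not mention one, so the two would have to be reconciled.
2. **The two worries pull against each other.** If no 1-month control score is collected, no between-group test at 1 month is possible and nothing is inflated. The error figures apply only if the score is collected in both arms. This is right, and it makes the figures conditional. It leaves the unnamed time point and the unequal collection wording untouched.
3. **Section 8 is ambiguous.** The parenthesis may belong mainly to the biomarkers, and one longitudinal comparison would also fit the sentence. Reading it as covering all three variables is the most natural, but not certain. If it covers only the biomarkers, the primary outcome has no analysis time anywhere, and one still has to be named.
4. **A full protocol or analysis plan may rank the times.** It may. But the article itself sets two times and a collection schedule that does not match them, so this is more than detail left for later.

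A reader might also infer that the 30% one-year dropout has to be re-based to 3 months. That does not follow: one year matches the longest secondary outcome, a one-year allowance would normally be conservative for a 3-month endpoint, and the documents give no 3-month figure.

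**Conclusion.** The concern holds in a limited form. The primary EHFScBS outcome has no stated time point. Section 8 most naturally compares it at 1 and 3 months without a primary. Section 6 fixes the follow-up score for controls at 3 months and does not clearly fix it for intervention patients who are not readmitted.

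The error of about 7% to 10% is not a property of the plan as written. It rests on three assumptions that the documents do not state: two-sided 5% tests, success at either time, and a correlation between 0 and 0.9. It also requires 1-month scores in both arms. What needs no assumption is that the sections do not agree on when the primary outcome is measured. The sample size of 210 is reproduced only as a single comparison, taking alpha as two-sided 5%. This should be corrected before data are seen.

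**What to change.** - **Sections 3.1 and 8:** name change in EHFScBS from discharge to 3 months after discharge as the single primary comparison. This is the only fixed follow-up time that Section 6 gives for controls, and counting from discharge removes the doubt about whether the months in Section 8 run from discharge or from the end of the intervention.
- **Section 6:** state that this score is taken in the same window for all patients in both arms, whether or not they have been readmitted. Scores taken at readmission can be kept as additional data.
- **1 month:** make it secondary if it is collected in both arms; otherwise delete it from Section 8.
- **Figure 1:** check its survey times against Section 6 and reconcile any difference.

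The cost is wording in the protocol and analysis plan, with no extra patients. Sites in the intervention arm would need a fixed 3-month assessment if they do not already have one. The downside is that an effect seen at 1 month alone would no longer count as success.

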### 2.2. Trial Design

We will conduct a cluster randomized controlled trial across different facilities to compare the efficacy of outpatient support by telephone and in person, as provided by a nurse.

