### 2.5. Randomization and Blinding

Eligible facilities will be gathered through open solicitation. The joint research institutions will be selected based on discussions among and comprehensive review by the internal meetings of this association. We will assign the intervention group (facility) and the control group (facility) at a 1:1 ratio through stratified randomization according to the volume of potential patients. Patients from each facility who provide their consent will be included as intervention subjects. Since the study involves a behavioral intervention without a potential placebo counterpart, it will be impossible to blind both investigators and participants to group allocations. However, data collection research assistants will be trained on consistent administration of measures and awareness of biases.

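### Facilities are randomised and the sample size assumes an ICC of 0.05, but the between-group methods in Section 8 are patient-level and make no provision for facility clustering

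*Protocol article*

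**What the plan says.** The design is clustered throughout. Section 2.2: "We will conduct a cluster randomized controlled trial across different facilities". Abstract: "A total of 40 facilities with certified HF nurses will be allocated to two-arm clusters at a 1:1 ratio". Section 2.5: "We will assign the intervention group (facility) and the control group (facility) at a 1:1 ratio", with facilities stratified by expected patient volume. Section 2.3 carries clustering into the planning: "The ICC was 0.05".

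Section 8 then lists the methods:

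- For EHFScBS, a Mann–Whitney "U-test will be used to compare the scores of the EHFScBS between the two groups". The sentence goes on to tie this comparison to patients' background characteristics.
- For readmission and symptom deterioration, a McNemar test, with a t-test and risk measures.
- For time to readmission, Kaplan–Meier curves "tested for significance using the log-rank test".
- For between-group differences in general, a Cox model and propensity score analysis.
- Multiple imputation for missing data, and adjustment for baseline patient characteristics where needed.

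The between-group comparison of change in self-care behaviour and in BNP/NT-proBNP is announced without a named test. The section does not mention facility, cluster, random effect, GEE, frailty or robust variance.

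**The concern.** When whole facilities are allocated, patients at one facility share staff, routines and case mix, so their outcomes are correlated. A standard patient-level test counts each patient as a full independent observation. It therefore understates the standard error of the arm difference, gives p-values that are too small and intervals that are too narrow. The error always runs in the direction that favours finding a difference.

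The article accepts in Section 2.3 that this correlation exists and then names an analysis that ignores it. Section 8 hands the data to a contracted analysis organisation, and Section 9 says the results will support policy recommendations, including on medical fees. An analyst who followed Section 8 literally would report results that look more certain than the design allows.

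**Working it through.** **Inputs from the documents.** 40 facilities at 1:1, so 20 per arm (Abstract). 210 patients, 105 per arm; difference 4, SD 8.5, power 80%, ICC 0.05, dropout 30% (Section 2.3).

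**Assumed, because not stated.** Two-sided 5% level and 95% intervals.

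**1. The plan's own figure.** Without clustering, n per arm = 2 × [8.5 × (1.96 + 0.842)/4]² = 70.9, so 71.

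- The design effect is DE = 1 + (m − 1) × ICC. With m = 142/40 = 3.55, DE = 1.1275 and 71 × 1.1275 = 80.1. Multiplying by 1.3 for dropout gives 104.1, so 105 per arm and 210 in total. This is the stated figure.
- Using m = 3.675 (DE 1.134) also gives 105.
- Leaving out the ICC and dividing by 0.7 gives 102 per arm, or 204, which is close but not equal.

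The stated 210 is thus consistent with clustering having been counted at the planning stage. How dropout was applied is a separate matter.

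**2. Design effect at the analysis.**

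- Enrolled: m = 210/40 = 5.25, so DE = 1 + 4.25 × 0.05 = 1.2125.
- After 30% dropout: m = 0.7 × 5.25 = 3.675, so DE = 1 + 2.675 × 0.05 = 1.134.

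An unadjusted standard error is too small by 1 − 1/√DE, which is 9% and 6%.

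**3. True error of an unadjusted patient-level EHFScBS comparison.** Type I error = 2 × [1 − Φ(1.96/√DE)]; coverage is its complement.

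| Patients per facility | DE | Type I error | Coverage of nominal 95% interval |
|---|---|---|---|
| 3.675 | 1.134 | 6.6% | 93.4% |
| 5.25 | 1.2125 | 7.5% | 92.5% |

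**4. Simulation check.** 20,000 trials per setting, 20 facilities per arm, ICC 0.05, no true difference.

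- Mann–Whitney, near-equal facility sizes: 6.3% (74 per arm) and 7.6% (105 per arm).
- Mann–Whitney, facility sizes varying with an assumed coefficient of variation of 0.8: 7.4% and 8.8%. Unequal sizes are plausible, since Section 2.5 stratifies by patient volume.
- A t-test on the 40 facility means from the same data: 4.8% to 5.0%. A simple facility-level analysis therefore restores the level.

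**5. Sensitivity to the ICC (equal sizes, other ICCs assumed).** The lowest value is at ICC 0.01 with m = 3.675: DE = 1.027, error 5.3%. The highest is at ICC 0.10 with m = 5.25: DE = 1.425, error 10.1%.

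**6. Other outcomes.** Section 2.3 gives its ICC for the EHFScBS sample size only. Nothing in the article allows the same calculation for readmission, time to readmission or BNP/NT-proBNP.

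**The case against.** The strongest reply is that this is a condensed article, that an analysis plan may exist, and that handling of clustering may be set out there. That would answer mere silence. But Section 8 names methods, and the standard Mann–Whitney, t-test and log-rank do not account for the randomised unit; they would have to be modified or replaced. The one adjustment it offers is at patient level and conditional on need, which does not stand in for a facility term.

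Four further objections limit what can be said, and they stand:

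- A reader might infer that Mann–Whitney is the primary analysis. The text does not support that: the sentence is qualified by patient background, and the comparison of change is given no test.
- A reader might infer that a claimed 5% error rate or 95% interval is broken. The article states no level, sidedness or confidence coefficient for this trial.
- A reader might infer that every named method assumes independent patients. McNemar is a test for paired data, so its fault here is different and the design effect does not describe it. Cox can carry a frailty term or robust variance, and propensity score analysis does not fix a variance estimator; the point is only that neither is given one.
- The inflation is moderate, because facilities contribute only about four to five patients each. The higher values need assumed unequal sizes or an assumed larger ICC.

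**Conclusion.** The concern holds as an inconsistency between design and analysis: clustering is recognised in Sections 2.2, 2.3 and 2.5 and absent from the methods in Section 8. For EHFScBS, at the article's own ICC and an assumed two-sided 5% level, an unadjusted patient-level comparison would run at about 6.6% to 7.5%, and somewhat higher with unequal facilities. This is an excess of 1.6 to 2.5 percentage points, systematic and in the anti-conservative direction. For readmission and BNP/NT-proBNP the direction is the same wherever outcomes are positively correlated within facilities, but the size cannot be stated.

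The documents do not support saying that the primary analysis is definitely invalid, since its test is not clearly named. They do support saying that Section 8, followed as written, offers no method that respects the randomised unit. That should be settled before outcome data are seen.

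**What to change.** In Section 8, state that all between-arm comparisons account for facility and for the volume stratum used in randomisation, and name the methods:

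- EHFScBS and BNP/NT-proBNP: a mixed model with a facility random intercept and small-sample correction, or an analysis of facility means. Name the chosen one explicitly for the primary change.
- Readmission proportions: GEE or mixed models with small-sample correction, in place of McNemar, which does not fit two parallel arms.
- Time to readmission: Cox with facility-robust variance or shared frailty, in place of the unadjusted log-rank test.
- Multiple imputation: include facility in the imputation model.

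State the significance level and sidedness in the same place.

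The cost is a change of wording. At ICC 0.05, intervals widen by √1.134 − 1 = 6% to √1.2125 − 1 = 10%, plus a little for the small-sample correction. The change itself needs no extra data or patients.
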